### Intervention components

#### Usual care arm

The usual care arm will undergo the first- and second-level assessment. Patients with HTN and/or DM in the control arm will also be referred to PHCs or encouraged to access their preferred health care facility.

#### Treatment arm

We propose to utilise existing healthcare resources such as PHCs, ASHA workers, NGOs, and family counselling centres, which are already functioning in the community, for the intervention. The package comprising five separate modules on general, behavioural, social, cognitive, and multiple interventions prepared by the research team based on information collected through quantitative, qualitative, and rapid systematic review of existing evidence will be applied based on the risk categorisation.

General interventions will be delivered to all participants included in the intervention arm. Behavioural, social, and cognitive interventions will be separately administered to participants based on the group they belong to. For the fourth group, that is, the multiple risk groups, interventions will be customised based on their priority needs. All the interventions are developed targeting the entire family.

### Overview of intervention

The intervention is delivered to participants based on identified risk categories.

#### Intervention implementation, general

General intervention is administered to all participants in the intervention arm. General information comprises the importance of treatment adherence and adequate control of chronic conditions. An overview of intervention components is provided in Table 2.

**Table 2 Tab2:** Overview of Interventions

**Participant Categories**	**Objectives**	**Interventions**	**Tools**	**Methods**
Behavioural risk group	To incorporate lifestyle modifications to manage diabetes and hypertension in patients	**Individual level** 1) Risk management strategies for alcohol consumption, smoking, sedentary lifestyle, and low-fat diet recipes, and specific monitoring strategies for salt, sugar, and oil intake. 2) Graded reduction strategies for alcohol consumption and smoking; Linking to de-addiction centres if necessary.	Healthy lifestyle- specific brochures, videos on anatomical explanation on unhealthy habits and its foreseeable effects, chronic condition-specific leaflets, and monitoring charts	Household visits by ASHA workers once in a month
		**Family level** 3) Obesity intervention programmes for potential patients by providing a customised diet plan.	Diet charts and recipe books	Information booklet-based family consultations by ASHA workers
		**Community level** 4) Community awareness generation regarding the effect of unhealthy habits and sedentary lifestyle on chronic conditions	Brochures, health calendars, and health-related videos	ASHA workers spend 10–15 minutes in community meetings to speak about healthy lifestyle
Social risk group	To bring about changes in individuals and families by promoting more social networks and ties with others in the community	**Family level** 1) Forming beneficiary groups of participants 2) Availing services such as free medicines, micro-pharmacy, doctor emergencies, and transportation facilities to hospitals	Brochures and handouts comprising details of already existing support systems	Individual- and family-level consultations and connecting to existing NGOs and other functionaries
		**Community level** 3) Awareness generation regarding support services, government welfare and health schemes, nongovernment organisations, and other informal provisions and resources	Beneficiary groups, and handouts with the details of agencies along with their address and phone number	Creation of beneficiary groups by ASHA workers, and distribution of brochures
Cognitive risk group	To modify the negative cognition of patients through cognitive techniques for better mental health	**Individual level** 1) Cognitive and behavioural steps, and referral to family counselling centres (FCCs)	Case management technique videos and awareness classes	FCC staff to provide therapy sessions, and ASHA workers to generate awareness on common mental health conditions
		**Family level** 2) Strategies to improve connections between family members 3) Community linkage for socially vulnerable patients	Increasing the frequency of visits to these vulnerable families	House visits by ASHA workers and encouraging frequent contacts

The major components of the intervention package include assessment, psychoeducation, risk-specific intervention, and linkage with emergency services.

### Intervention content

Brochure for health education with information regarding the importance of medication adherenceInstructions to families to monitor treatment adherence and medication complianceSteps on how families can support (physically and emotionally) through reminders, positive encouragement, etcCommon strategies for behavioural risk management, such as the provision of a diet chart, healthy recipe book, health calendar, which is to be mounted on the kitchen wall, and pamphlets for simple and effective cognitive strategies such as relaxation techniques. ASHA workers will be responsible for implementing general interventions. They will explain in detail the aforementioned four strategies before handing out the brochures and pamphlets. The research team and CHSWs will perform monitoring and coordination during the intervention. One-day training will also be provided to all ASHA workers prior to the implementation of interventions.

In addition to the general intervention, participants in the treatment arm will be administered risk-group specific interventions as follows.

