### Study design and setting

This is a two-arm cluster randomised controlled trial (RCT) designed to be executed in patients with DM or HTN in association with government-run PHCs and the existing public health ecosystem in Kerala, India. This study will be conducted in Ernakulam district, Kerala, India, with active support from University of York, United Kingdom, and University of Melbourne, Australia. The Ernakulam district is administratively divided into seven main revenue divisions, and Aluva is one of them [14]. The Aluva division is further divided into different units called panchayats (with approximately 25,000–30,000 people residing in each panchayat and each panchayat is further divided into different wards with approximately 1000 to 1500 people residing in each of them), and one panchayat from the Aluva division is selected for the intervention. PHCs and ASHA workers assigned to these geographical units will assist the execution of the intervention. ASHA workers are a network of community health workers who are often selected from the same community; thus, they have the acceptance and trust of the community people. A list of ASHA workers consenting to participate in this study will be prepared, and 10 of them will be randomly selected using computer generated random numbers for providing the intervention. Their assigned wards will be considered as intervention clusters for the current trial. A list of patients with DM or HTN from the selected wards will be obtained from the PHC registry through ASHA workers, and household interviews will be conducted for data collection. Three data collection time points are planned for both the arms: one at baseline and then after 6 months and 12 months after baseline.

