Two levels of randomization will be employed in this study. Of the 10 ASHAs, 5 will be randomly allocated either to the treatment intervention arm (Swasthya intervention) or the usual care arm (no interventions other than detailed assessments). Computer-generated random numbers generated by an independent person who is not involved in the study will carry out the randomization of the ASHA workers to either group. Randomization of ASHAs and their clusters will be performed only after the collection of complete baseline data. Their assigned wards will be considered as intervention clusters for the current trial. To eliminate the possibility of contamination, these two groups of ASHA workers will be given training and orientation separately and each of them will be concealed by the group to which they belonged. Independent persons will do the outcome assessment and manage the data to ensure blinding to the Intervention content and its processes. The data analysts will receive the data only after locking the database.

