#### Human resources for the assessment

ASHA workers will conduct the first-level (verbal screening) and second-level assessments (mobile App based), followed by the detailed baseline assessment performed by CHSWs. Along with ASHA workers, JPHNs will conduct clinical assessments including the measurement of blood pressure (BP) and blood sugar levels. The primary and secondary outcome measurements for determining the effectiveness of the intervention will be performed by a separate group of CHSWs in order to blind the hypothesis from the intervention team. The intervention will be functionally and geographically coordinated by CHSWs appointed in PHCs during the project implementation period.

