Programme evaluation	Group evaluation	Usefulness of group sessions, Utilisation of NGO services	4 month	8 month	12 month
	Other evaluation	Usage of health calendar, diary, etc.	4 month	8 month	12 month

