#### Secondary outcomes

Secondary outcomes include optimal health indicators such as (a) increased compliance to medication as reported by family members; (b) a reduction in the quantity of salt, oil, sugar, and meat bought in a month; (c) an increased number of healthy food items prepared in the household in a month; (d) sticking to the diet chart and health calendar; (e) a reduction in or abstinence from alcohol consumption; (f) engagement in at least one physical activity; (g) increased engagement with family, friends, and church groups; (h) getting back to professional or academic life and attending work or school regularly; and (i) attainment of appropriate BMI(< 25 kg/m^2^). In addition, the outcomes included attending at least one group meeting, increased linkage with the community, formal and informal interactions with the community, utilisation of nongovernmental organisation (NGO) services, regularity in hospital visits, and decreased depression and anxiety.

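### The outcome assessors are said to be blind to intervention content, yet the outcomes assigned to them include questions about that content

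*Protocol article*

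**What the plan says.** All references are to the protocol article.

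- **The blind.** Study design and setting: "Independent persons will do the outcome assessment and manage the data to ensure blinding to the Intervention content and its processes".
- **Who measures.** Human resources for the assessment: "The primary and secondary outcome measurements for determining the effectiveness of the intervention will be performed by a separate group of CHSWs". The stated reason there is to keep the hypothesis from the intervention team, which is a different blind from the one above.
- **What they measure.** Secondary outcomes lists "sticking to the diet chart and health calendar", along with attending a group meeting and using NGO services.
- **When.** Table 1 puts the programme evaluation, including "Usage of health calendar, diary, etc", the usefulness of group sessions and NGO use, at months 4, 8 and 12. Month 12 is also when tobacco use, DASS, adherence, blood pressure and glucose are due.
- **Where.** Study design and setting: "household interviews will be conducted for data collection". The next sentence adds "Three data collection time points are planned for both the arms".
- **What is in the home.** Intervention content, as part of the general package: a "health calendar, which is to be mounted on the kitchen wall", with a diet chart, recipe book and pamphlets. Treatment arm: "General interventions will be delivered to all participants included in the intervention arm".
- **What usual care receives.** Study design and setting gives that arm nothing beyond assessment. Usual care arm adds only referral or encouragement to attend a health facility. The Methods part of the abstract, however, says the control arm receives the general intervention.

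**The concern.** Using separate staff for outcome measurement keeps assessors apart from delivery. It does not keep them blind if their own questionnaire asks about the calendar, the diet chart, group meetings and NGO services, or if those materials are visible where they work. Because the ward is the unit of allocation, what an assessor learns from one participant applies to every other participant in that ward.

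At stake is how far the results can be called blinded. Tobacco abstinence is a primary outcome and is collected by questionnaire. DASS is self-reported, and medication compliance is reported by family members. An interviewer who knows the arm can probe and code such answers differently, most plausibly in favour of the intervention. A report that repeated the claim of ensured blinding would lead readers to discount that risk.

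**Working it through.** The article gives no figure for blinding or assessor bias, so there is nothing to reproduce. The check sets the statements side by side.

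1. **Same assessors, both sets of outcomes.** Human resources for the assessment assigns primary and secondary outcomes to one separate CHSW group. Secondary outcomes includes calendar and diet-chart use, group attendance and NGO use. Together, the group that records the primary outcomes also asks about intervention materials and activities. This conflicts with being blind to intervention content, wherever the visit takes place.

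2. **Same time point.** From Table 1:

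| Item | 6 months | 12 months |
|---|---|---|
| Blood pressure, glucose | yes | yes |
| Treatment adherence | yes | yes |
| Tobacco (behavioural questionnaire) | no | yes |
| DASS | no | yes |
| Programme evaluation (calendar, diary, group sessions, NGO use) | no (months 4 and 8) | yes |

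The programme evaluation meets outcome collection at month 12 only. That is the only follow-up at which tobacco and DASS are measured.

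3. **Visible materials, conditional on place.** The calendar is meant for the kitchen wall. If the 6- and 12-month visits are household interviews, the assessor may see it before asking anything. Baseline is unaffected, because allocation follows complete baseline data collection.

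4. **Spread by ward.** 1452 participants / 10 wards = 145.2, so about 145 people share each allocation. One disclosure can reveal the arm of the rest to any assessor who sees more than one home in that ward.

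5. **Dependence on what controls receive.** Steps 1 to 3 identify the arm through the calendar and diet chart only if usual care lacks them. Study design and setting, Usual care arm, Treatment arm and Intervention implementation, general all point that way; the abstract does not. If controls also had the general package, those two items would no longer separate the arms, although risk-specific materials, group activity and NGO linkage would still differ.

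**The case against.** Several objections have force.

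- **The abstract conflicts on the control arm.** This stands as a condition on the point, and the passages must be reconciled.
- **Home follow-up is inferred.** The household-interview sentence comes straight after the one on obtaining patient lists, and no text states where the 6- and 12-month measurements take place. So the wall calendar is a conditional mechanism. The overlap between assessor and outcome list does not depend on it.
- **Nobody is named as collecting the programme evaluation.** Correct: that it shares the assessor's form cannot be assumed. Calendar and diet-chart use, group attendance and NGO use are nevertheless secondary outcomes in their own right, and those are assigned to the assessors.
- **Blood pressure is not self-report.** It is read on an electronic monitor and two readings are averaged. A reader might infer that the blind fails with equal consequence for every outcome; the document does not support that. The room for assessor influence on blood pressure is smaller.
- **Participants and families know what they received.** True, so assessor blinding could protect self-reported outcomes only in part. That is a further reason not to call the blinding ensured.
- **Item order and assessor scripts belong in a manual.** Agreed, and their absence is not the point. The point is that a stated property conflicts with stated procedures.

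**Conclusion.** The point holds as a contradiction between the blinding statement and the outcomes assigned to the assessors. It is firmest at month 12. It matters most for tobacco abstinence, DASS and adherence, and less for blood pressure. It assumes that usual care receives no general package; the visible-calendar part further assumes that follow-up takes place in the home.

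No magnitude can be derived. A reader might attach one: under a normal model with mean systolic pressure at the 140 cut and SD 18, a 2 mmHg assessor effect moves the share below 140 by Phi(2/18) - 0.5 = 4.4 percentage points. The document gives neither the mean, the SD nor the bias, a mean at the cut is the most sensitive choice, and nothing in the text supports such an effect with an electronic monitor. The same applies to any assumed shift in reported tobacco abstinence. Nor does the text show that the final report will claim a blind it did not have. It shows only that the present wording promises more than the procedures deliver.

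**What to change.** 1. At each follow-up visit, record and lock blood pressure and glucose first, then the questionnaires Table 1 schedules for that visit: adherence at 6 and 12 months, tobacco and DASS at 12 months only. Ask nothing about the calendar, diet chart, diary, group sessions or NGO use until these are locked.
2. Put those items last or on a separate form. Where possible, have them collected by existing project staff who are neither the outcome assessors nor the ASHA workers delivering the intervention, so that deliverers do not score their own work.
3. Have the assessor record a guess of the arm once the primary outcomes are locked.
4. Reword the blinding sentence in Study design and setting to say that assessors are not told the allocation, and describe the self-reported outcomes as not reliably blinded.
5. Reconcile the abstract with the Methods on what the control arm receives.

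The cost is minor form re-ordering and some logistics for the separate form. Re-ordering does not hide materials already on display, so the rewording in step 4 is needed as well.

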#### Intervention implementation: behavioural

Behavioural interventions are proposed for lifestyle modifications to manage DM and HTN and are widely used to gain control over chronic illnesses [15]. This intervention particularly focuses on bringing changes in alcohol consumption/dependence, smoking, physical inactivity/sedentary lifestyle, and improper food habits/uncontrolled diet. In addition, respondents will be linked to de-addiction centres if necessary.

#### Intervention implementation: social

Social interventions are proposed for improving treatment adherence, enhancing social cohesion, and improving social connections. Support from family and friends [16, 17], health centres [18], and peer or community [16, 17] are identified as significant contributors to the management of chronic illnesses. Table 2 lists the interventions provided to participants in this group.

#### Intervention implementation: cognitive

Cognitive interventions are proposed wherein cognitions are modified to aid in attaining better mental health. The emotional and psychological well-being of a patient is vital for the management of chronic illnesses [18]. Cognitive realisation for the need and importance of adhering to medication is necessary. Cognitive interventions will include (1) video interventions highlighting risk factors associated with various chronic conditions, symptoms of anxiety and depression, and cognitive and behavioural steps to manage anxiety and depression and (2) strategies to improve social cohesion and communication, such as encouraging common meals, family routines, etc. Patients with severe cognitive dysfunction will be referred to the nearest family counselling centre (FCC).

##### Personnel involved

ASHA workers will initiate the implementation because they already have an established trusting relationship with participants and can serve as an essential link to reach out to the community. During the intervention phase, ASHA workers will meet study participants once in a month to assess the compliance to the intervention programme and participation. Other personnel include NGOs, community clubs, youth volunteers, and FCCs funded by the central social welfare board. Monitoring and coordination will be conducted by the research team and CHSWs. Two-day training will be provided to all ASHA workers prior to the implementation of the interventions.

##### Materials for intervention

Dietary charts, health calendars, brochures, and pamphlets constitute a significant part of the intervention. In addition, a mobile application developed with the help of a software developer will be a main part of the assessment and categorisation of participants.

### Sample size

In the community, 36.33% people aged more than 30 years were found to have HTN and/or DM [9]. Thus, this cluster RCT will include 1452 participants and their families (726 patients in each arm). Trained and certified project staff will collect baseline data by using study questionnaires. Project staff, under the supervision of the principal investigator, will complete data entry into computer systems. The data will be collated, cleaned, and analysed centrally. Furthermore, the accuracy of data entry in randomly selected fields will be independently checked by the principal investigator of the study.

### Statistical analysis

Data will be analysed on the basis of the intention to treat principle. Changes observed from the baseline and at follow-up will be compared between the intervention and usual care groups. All data will be de-identified using a unique ID to ensure the confidentiality of information. Upon implementation of the intervention, follow-up measurements will be taken at 6 and 12 months from the baseline. Data will be generated from standardised questionnaires and assessment procedures. Baseline characteristics will be described using means (with standard deviations) or frequencies based on the type of variable. The mean difference between the groups will be examined to understand the effects of the intervention. Mixed effect analysis of covariance will be employed to test for interactions between time (pre and post) and group (intervention or usual care), and partial eta squared (ηp^2^) will be reported as a measure of effect size. The comparisons of variables will be adjusted for potential confounders. The intention-to-treat analysis will be used to observe changes occurred throughout the year during follow-up in participants assigned to the Swāsthya intervention and usual care. The effect attributable to the intervention will be estimated by calculating mean differences between the groups at each of the follow-up points (at the baseline and at 6 and 12 months after the baseline; adjusted odds ratios for dichotomous outcome variables at 95% confidence intervals). Precautions will be taken to rule out the potential interaction effects between the Swāsthya and usual care groups. Software-assisted multiple imputation methods up to five times will be used to deal with missing values. All statistical analyses will be performed using STATA-14 and R software. The effectiveness of the intervention model will be ascertained 1 year after the completion of the study, and the model in itself will also be made public. Information on the study will be available on the website of the college as well as reported in scientific journals and at scientific conferences.

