**Methods:**

A cluster randomised controlled trial (RCT) in selected participants will be conducted involving additional assessments prior to the baseline assessment. The assessment will identify and categorise patients into four risk groups, namely behavioural, social, cognitive, and multiple, based on dominant risks identified. Eligible participants will be randomly allocated (at a ratio of 1:1) into the intervention or control arm. The intervention arm will receive social, behavioural, and cognitive or multiple interventions corresponding to the identified risk groups, whereas the control arm will receive general intervention. Both the groups will be followed up at 6 months and 12 months post baseline to measure outcomes. The primary outcome will be the control of HTN and DM, and secondary outcomes include decreased depression and anxiety and improved functioning, social cohesion, and social network linkages. The sustainability and scalability of this intervention will be assessed through cost effectiveness, acceptability, and user friendliness of the integrated approach by performing a qualitative evaluation.

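### Ten wards are randomised, but the stated analysis names no ward or cluster term for any arm comparison; if ward is ignored, type I error could be materially inflated

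*Protocol article*

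**What the plan says.** The body of the protocol article is clear about the unit of allocation. Under Study design and setting, ten ASHA workers are drawn at random from those who consent, and "Their assigned wards will be considered as intervention clusters for the current trial". Then "Of the 10 ASHAs, 5 will be randomly allocated either to the treatment intervention arm" or to usual care, read here as 5 per arm. The same section adds: "Randomization of ASHAs and their clusters will be performed only after the collection of complete baseline data". Under Sample size: "Thus, this cluster RCT will include 1452 participants and their families (726 patients in each arm". No ICC or design effect is given there.

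The Statistical analysis section names the test: "Mixed effect analysis of covariance will be employed to test for interactions between time (pre and post) and group (intervention or usual care". It adds that "partial eta squared (ηp^2^) will be reported as a measure of effect size". The effect credited to the intervention is then to be estimated by between-group mean differences, with adjusted odds ratios and 95% confidence intervals for dichotomous variables. The time points listed for this are baseline, 6 months and 12 months. Adjustment is for potential confounders. The section mentions no ward, ASHA worker, cluster, ICC, robust variance or cluster-level summary.

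The primary outcomes are blood pressure and fasting glucose below stated thresholds, and abstinence from smoking or tobacco. As worded, these are dichotomous.

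**The concern.** Patients in one ward share an ASHA worker and a community, and in the intervention arm they receive the programme through that one worker. Their outcomes are therefore likely to be correlated, and the evidence about the arm effect comes from differences among ten wards rather than among 1452 independent people. An analysis that follows the section as written, with time, group and confounders only, would give standard errors that ignore the randomised unit. Confidence intervals would be too narrow and p-values too small whenever wards differ for reasons unrelated to the intervention.

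This matters most for the adjusted odds ratios, which are the stated summary for the dichotomous primary outcomes and for which no mixed or clustered structure is mentioned.

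**Working it through.** **1. Inputs.**
- From the article: 10 wards and 1452 patients, so mean ward size m = 1452/10 = 145.2. With 5 wards per arm, the between-ward degrees of freedom are 10 − 2 = 8.
- Assumed: two-sided 5% tests (the article gives only 95% intervals) and ICC from 0.001 to 0.05 (none is given).

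**2. The plan's own figure.** The only numerical input offered for 1452 is a prevalence of 36.33%, and 1452 cannot be derived from that alone. A one-sample precision formula gives 1.96² × 0.3633 × 0.6367 / 0.035² = 725.4, which rounds up to 726 and doubles to 1452. The 3.5-point margin is not in the article, so this is only a possible origin. For scale, 726 per arm under individual randomisation would have 80% power for a rise of about 7.2 points from 36.33%. No allowance for clustering is visible.

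**3. Comparison at one follow-up visit, ward ignored.** DEFF = 1 + (145.2 − 1) × ICC. Real type I error = 2 × [1 − Φ(1.96/√DEFF)]. Effective N = 1452/DEFF. The correct interval, using ward variance and t on 8 df (2.306 in place of 1.96), is wider by √DEFF × 2.306/1.96.

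| Assumed ICC | DEFF | Effective N | Real type I error | Correct CI wider by |
|---|---|---|---|---|
| 0.001 | 1.14 | 1269 | 6.7% | 1.26 |
| 0.005 | 1.72 | 844 | 13.5% | 1.54 |
| 0.01 | 2.44 | 595 | 21% | 1.84 |
| 0.02 | 3.88 | 374 | 32% | 2.32 |
| 0.05 | 8.21 | 177 | 49% | 3.37 |

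**4. The time-by-group test, ward ignored.** Within-person change removes any ward difference that is constant over time, so the table above does not apply directly. With cluster autocorrelation c and within-person correlation r (total variance 1), the change score has ward variance 2 × ICC × (1 − c) and person variance 2 × (1 − ICC) × (1 − r). Simulating 20,000 trials with 10 wards of 145 and r = 0.5 (assumed) gave these rejection rates for a person-level test of change:

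| Assumed ICC | c = 1 (fully stable wards) | c = 0.8 | c = 0.5 |
|---|---|---|---|
| 0.01 | 5% | 12% | 21% |
| 0.02 | 5% | 19% | 32% |
| 0.05 | 5% | 33% | 50% |

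A hand check at ICC 0.01 and c = 0.8: the ICC of the change is 0.002/(0.002 + 0.495) = 0.0040, DEFF = 1 + 144 × 0.0040 = 1.58, and 2 × [1 − Φ(1.96/√1.58)] is about 12%, which agrees.

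**5. Few clusters.** If ward is modelled but the statistic is referred to the normal distribution, P(|t₈| > 1.96) = 8.6%. The same simulations gave 8.3% to 8.9% for a ward-level test referred to 1.96, and 4.8% to 5.2% with t on 8 df.

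**6. Baseline.** Statistical analysis counts baseline among the points at which the intervention effect is estimated. Study design and setting places randomisation after baseline collection is complete. A baseline difference between arms therefore cannot be an effect of the intervention.

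**The case against.** The strongest reply is that this is a condensed article, that the analysis plan is not shown, and that a model described as mixed may well contain a ward random effect. The article calls the trial cluster randomised throughout. A reader might infer that the planned model is definitely a person-level one with no ward term. The text does not support that: the random effects are unspecified. The pre/post-by-group layout and partial eta squared suggest a between-within design on persons, but they do not establish it. That part of the reply stands.

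It does not dispose of the point. The section is specific about factors, interaction, effect-size measure, adjustment, number of imputations and software, yet silent on the unit that was randomised. The word mixed is attached only to the ANCOVA, not to the odds ratios. Small-sample degrees of freedom alone could fairly be left to an analysis plan, so the 8.6% figure is supporting evidence only.

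The reply is also right about size. A reader might carry the 21% to 49% figures over to the time-by-group test, or conclude that the intervals are bound to be far too narrow. Neither follows: stable ward effects cancel in that test, and at an ICC of 0.001 the single-visit error is only 6.7%.

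Three further inferences are not supported:
- The article says "Software-assisted multiple imputation methods up to five times will be used to deal with missing values". It does not describe the imputation model, so it cannot be said that wards are left out of it.
- The ANCOVA suits continuous means, but the same section provides adjusted odds ratios, so the dichotomous outcomes are not left without an analysis.
- The abstract says "Eligible participants will be randomly allocated (at a ratio of 1:1) into the intervention or control arm". The same abstract calls the trial cluster randomised and the body randomises ASHA workers, so this is loose wording and not evidence of a person-level analysis.

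**Conclusion.** The point holds in conditional form. Ten wards are randomised, and no stated arm comparison is said to account for ward. If ward is ignored, the comparisons that bear on the dichotomous primary outcomes would have a real type I error of about 7% to 49% over the assumed ICC range. The time-by-group test would range from no inflation with fully stable wards to about 12% to 33% at ICC 0.01 to 0.05, given cluster autocorrelation 0.8 and within-person correlation 0.5.

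All these sizes rest on assumed correlations, equal ward sizes and a split of 5 wards per arm. What needs no assumption is that the section omits the randomised unit, and that listing baseline as a point of intervention effect contradicts the order of randomisation. The omission goes to the validity of the main result, so it should be settled before the analysts receive the data.

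**What to change.** Amend the Statistical analysis section to state that every arm comparison accounts for ward, including the odds ratios for control status and tobacco abstinence, and adjusts for the participant's baseline value. Either of two routes would do:
- a two-stage ward-level analysis with covariate adjustment, referred to t on 8 df; or
- a mixed model with a ward random effect, plus ward-by-time or participant effects where visits are modelled together, and a small-sample reference suited to 10 clusters. Examples are Satterthwaite or Kenward-Roger degrees of freedom for linear models, or a permutation test over ward allocations.

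If the existing mixed model was always meant to include ward, saying so and naming the reference distribution is enough for that test; the odds ratios still need the same statement. Remove baseline from the time points at which the intervention effect is estimated.

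The change is to wording only, and both named packages can fit these models. The cost is wider intervals, by a factor of about 1.26 to 3.37 over the assumed ICC range for single-visit comparisons. They would show the precision that ten wards can actually give.
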